# Simultaneous reduction of flow and fraction of inspired oxygen (FiO_2_) versus reduction of flow first or FiO_2_ first in patients ready to be weaned from high-flow nasal cannula oxygen therapy: study protocol for a randomized controlled trial (SLOWH trial)

**DOI:** 10.1186/s13063-019-4019-7

**Published:** 2020-01-14

**Keywords:** Adult, High-flow nasal cannula, Protocol, Weaning

## Abstract

**Background:**

High-flow nasal cannula (HFNC) oxygen therapy has been widely used in critically ill patients. Despite the effectiveness of HFNC as a treatment, optimal methods to withdraw HFNC after recovery from preexisting conditions have not been investigated to date. In this study, we will evaluate the safety and efficacy of simultaneous reduction of flow and fraction of inspired oxygen (FiO_2_) compared with sequential reduction of either flow first or FiO_2_ reduction first in patients with HFNC.

**Methods/design:**

This is a prospective, investigator-initiated, randomized controlled trial with three experimental intervention groups. A total of 100 adult patients receiving HFNC and satisfying weaning criteria will be enrolled and randomly assigned to one of the following groups: flow reduction (FR) first, FiO_2_ reduction (OR) first, or simultaneous reduction (SR). In the FR group, flow will be reduced first by 10 L/min/h. When it reaches 20 L/min, FiO_2_ will then be reduced by 0.1 /h until it reaches 0.3. In the OR group, the FiO_2_ will be gradually reduced first by 0.1 /h until it reaches 0.3, then flow will be reduced by 10 L/min until it reaches 20 L/min. Finally, in the SR group, both the flow and FiO_2_ will be gradually reduced simultaneously by 10 L/min and 0.1/h, respectively. Weaning will proceed only when patients satisfy the weaning criteria at every weaning point. When the HFNC weaning-off targets are reached (20 L/min and 0.3 for flow and FiO_2,_ respectively), the patient will be transferred to conventional oxygen therapy (mainly low-flow nasal prongs). The primary outcome is the time to successful weaning from HFNC for 24 h. Secondary outcomes will include the success or failure rate in weaning off HFNC and changes in arterial blood gas analyses, intolerance rate, length of hospital stay, and in-hospital mortality.

**Discussion:**

This study will be the first clinical trial to investigate the safety and efficacy of three different methods of weaning in adult patients receiving HFNC. Once this study is completed, we expect to be able to suggest the better strategy for withdrawal of HFNC based on the results.

**Trial registration:**

ClinicalTrials.gov, NCT03845244. Registered on 19 February 2019.

## Background

The heated and humidified high-flow nasal cannula (HFNC) has become an increasingly popular choice of therapy due to the potential complications of invasive ventilation [1, 2] and the frequent uncomfortable or life-threatening adverse effects that are produced in non-invasive ventilation (NIV) [3]. The HFNC allows modification of only two variables: the percentage of oxygen being delivered and the rate of gas flow [4]. Numerous well-designed studies have been conducted into the use of the HFNC in the treatment of critically ill patients, and HFNC is now widely used in the treatment of patients with various diagnoses including acute hypoxemic respiratory failure or acute respiratory distress syndrome (ARDS) [5, 6], and is used in post-extubation treatment [7–9], post-cardiothoracic surgery respiratory distress [10, 11], and respiratory compromise induced by heart failure [12, 13]. While studies are being conducted to determine both the optimal technique for HFNC delivery and the clinical setting in which it is most useful, the best strategy for weaning from HFNC remains unknown. It has also not been established at what point a patient should be considered stable enough to attempt to start withdrawing the HFNC.

Similarly, several limited studies have been conducted on strategies for weaning from NIV [14–16]. Lun et al. compared stepwise withdrawal to immediate withdrawal of NIV [16] and included 35 and 25 patients in the stepwise and immediate withdrawal groups, respectively. The rates of successful weaning were 74% for stepwise and 56% for immediate withdrawal, though the difference was not statistically significant (*p* = 0.139) [16]. Based on this result, the British Thoracic Society and Royal College of Physicians (BTS/RCP) recommend a protocol using stepwise reduction in NIV, which takes 4 days for weaning.

To the best of our knowledge, there is only one study into weaning protocols for the HFNC, which was conducted within a pediatric intensive care unit (ICU) [17]. The authors suggested a “holiday” weaning protocol. In the holiday protocol, patients scoring less than or equal to 6 qualified for a HFNC holiday trial on low-flow nasal cannula settings. Patients with a respirator assessment score (RAS) of 7 or 8 had HFNC flow decreased by half, and patients scoring more than 8 remained on current settings and were reassessed. If their RAS remained less than 6, a holiday patient stayed on a low-flow nasal cannula and continued traditional weaning based on oxygen saturations. If the RAS was 6–8, the patient was put on half the amount of flow and scoring was repeated. If the repeat RAS was greater than 8, holiday patients returned to initial settings. Out of 133 patients, 119 (89.5%) successfully weaned to low-flow nasal cannula within four holiday attempts, and 14 (10.5%) failed to be weaned. Though the holiday weaning method seems efficient, we have some concerns relating to its clinical application. First, this study was not designed for comparison of different methods of HFNC withdrawal. Second, there is a lack of detailed information about HFNC application and the risk of atelectotrauma. Last, this study included only children. This makes it hard to extrapolate to adults with HFNC. We are conducting this randomized controlled trial (RCT) to investigate the safety and efficacy of simultaneous reduction of the two variables compared to sequentially reducing either the flow first, or the fraction of inspired oxygen (FiO_2_) first for the withdrawal of the HFNC in adult patients who are stable and ready to be weaned.

## Methods/design

### Hypothesis

The time to weaning from the HFNC will be shorter in the simultaneous reduction group compared to the group having flow or FiO_2_ reduction first, without increasing the weaning failure rate.

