### Types of interventions

After randomization, the participants will undergo FR, OR, or SR strategies for weaning off the HFNC. In the FR group, flow will gradually be reduced by 10 L/min/h. When it reaches 20 L/min, FiO_2_ reduction will then begin at 0.1 /h until it reaches 0.3. In the OR group, FiO_2_ will gradually be reduced by 0.1 /h until it reaches 0.3. At this point, flow will be reduced by 10 L/min/h until it reaches 20 L/min. Finally, in the SR group, both flow and FiO_2_ will be gradually reduced simultaneously at a rate of 10 L/min and 0.1 /h, respectively, until they reach the HFNC weaning-off targets (20 L/min for flow and 0.3 for FiO_2_). Weaning will proceed only when the patient satisfies all the weaning criteria at every weaning point. When flow and FiO_2_ reach weaning-off targets, the patient will be transferred to conventional oxygen therapy, such as low-flow nasal prongs.

We have followed the Standard Protocol Items: Recommendations for Interventional Trials (SPIRIT) 2013 statement, which defines the standard protocol items for clinical trials [18] (see Additional file 1). The study algorithm is depicted in Fig. 1 and the SPIRIT schedule is shown in Fig. 2.

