### Outcome measures

The primary outcome is time to successful weaning from HFNC after 24 h of conversion to conventional oxygen therapy. The secondary outcomes will include the success or failure to wean off HFNC (within and after 24 h of conventional oxygen therapy), changes of arterial blood gas analyses (PaO_2_, PaCO_2_, and pH), intolerance rate, length of hospital stay, and in-hospital mortality.

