### Sample size calculation

It is difficult to calculate the target number of patients, because this is the first RCT evaluating the best strategy for weaning off the HFNC. Considering that 30 patients were compared in the NIV weaning protocol study, we estimate that a total of 90 participants, 30 in each group, would be needed. A total of 100 participants will be recruited in anticipation of a 10% dropout rate in each group based on the recent HFNC weaning study [17]. We have prepared for one interim analysis at the time when half of the subjects have completed the study.

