### Statistical analyses

Statistical analyses will be performed on both a per-protocol (PP) and an intention-to treat (ITT) basis. For the PP analysis, all participants who complete the study will be included to evaluate the primary and secondary outcomes. For the ITT analysis, all participants enrolled and randomized to one of the three groups will be included. In the interim analysis, if the *P* value is < 0.003, we will stop the study early, accepting the significance of the outcome. If not, we will recruit the remaining half of the subjects. Sub-group analysis according to the respiratory failure type (hypoxemic or hypercapnic) is planned. Unless otherwise specified, continuous variables will be expressed as mean plus standard deviations or median and categorical variables as percentages. Student’s *t* test will be used to compare continuous variables; the chi-square or Fisher’s exact test will be used to compare categorical variables. Unless otherwise stated, all tests are two-sided and performed at the 0.05 significance level. Analyses will be performed using SPSS 20.0 (IBM Corp., Armonk, NY, USA).

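### The hypothesis makes a no-worse claim on weaning failure, but the only stated analysis is a two-sided test of difference, which cannot support that claim at about 30 per arm

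*Protocol article*

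**What the plan says.** The Hypothesis section has two parts: weaning will be shorter with SR than with flow reduction first (FR) or FiO2 reduction first (OR), and this will happen "without increasing the weaning failure rate". Outcome measures places failure among the secondary outcomes: "The secondary outcomes will include the success or failure to wean off HFNC". Under Statistical analyses, "the chi-square or Fisher’s exact test will be used to compare categorical variables", and, unless otherwise stated, "all tests are two-sided and performed at the 0.05 significance level". The article gives no other analysis for failure.

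The Sample size calculation section says that "a total of 90 participants, 30 in each group, would be needed". It takes this from the size of an NIV weaning study and uses no effect size, power or margin. Recruitment is set at 100 to allow for 10% dropout.

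**The concern.** The failure clause says that one arm is no worse than the others. A two-sided test of difference addresses another question. It can give evidence that rates differ, but when it does not reject, the data may fit equality, a modest excess or a large one. The hypothesis and the stated test therefore do not match, and a more detailed plan that followed the stated test would inherit the mismatch.

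At stake is the safety half of the trial's conclusion. If SR proves faster and the failure comparison is not significant, the wording of the hypothesis invites a report of faster weaning with no more failures. At this sample size the data could look like that even if SR substantially raised the failure rate.

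**Working it through.** **Inputs**
- 30 evaluable per arm and 100 recruited, about 33 per arm (Sample size calculation).
- Two-sided 0.05, chi-square or Fisher (Statistical analyses). Pairwise comparisons of SR with one sequential arm are assumed.
- Comparator failure rate, lower assumption: in the pediatric HFNC study, "14 (10.5%) failed to be weaned" (Background); 14/133 = 10.5%.
- Comparator failure rate, upper assumption: 26%, that is 100% minus the 74% success of stepwise NIV withdrawal (Background).

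**The plan's own figures.** 90/(1 − 0.10) = 100, as stated. No power figure is given, so there is none to reproduce. The p value quoted for the NIV study also reproduces: 26/35 against 14/25 successes gives an uncorrected chi-square p = 0.139. An 18-point gap at 35 against 25 patients was thus not significant.

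**Power for a doubling, normal approximation.** With p1 = 0.105, p2 = 0.21, n = 30 and mean rate 0.1575:

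z = [|p2 − p1|√n − 1.96√(2 × 0.1575 × 0.8425)] / √(p1(1 − p1) + p2(1 − p2)) = (0.575 − 1.010)/0.510 = −0.85, so power is 19.7%.

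**Exact enumeration.** This sums the binomial probabilities of all outcome pairs at which the test rejects.

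| Comparator v SR | n | Fisher | Chi-square |
|---|---|---|---|
| 5% v 10% | 30 v 30 | 1.9% | 10.6% |
| 10.5% v 21% | 30 v 30 | 10.5% | 20.1% |
| 10.5% v 21% | 33 v 33 | 12.6% | 21.9% |
| 10.5% v 21% | 60 (FR and OR pooled) v 30 | 22.9% | 29.3% |
| 15% v 30% | 30 v 30 | 19.2% | 28.1% |
| 20% v 40% | 30 v 30 | 29.8% | 39.2% |
| 26% v 52% | 30 v 30 | 44.0% | 54.5% |
| 26% v 52% | 33 v 33 | 51.3% | 61.7% |

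At 30 per arm, a doubling from 10.5% is missed in 100 − 20.1 = 79.9% (chi-square) to 100 − 10.5 = 89.5% (Fisher) of trials. From 26% it is missed in 45.5% to 56.0%. Starting from 10.5%, 80% power is reached only when the SR rate is about 42%. Detecting 10.5% v 21% with 80% power would take 188 per arm.

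**Precision.** With equal true rates, the 95% half-width is 1.96√(2p(1 − p)/n):
- p = 0.105: 1.96√(2 × 0.105 × 0.895/30) = 0.155, or 15.5 points.
- p = 0.26: 1.96√(2 × 0.26 × 0.74/30) = 0.222, or 22.2 points.

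At 10.5% in both arms, an SR rate near 10.5 + 15.5 = 26% would not be excluded.

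**Example.** Observed failures of 3/30 and 6/30 give Fisher p = 0.47 and chi-square p = 0.28. The Newcombe 95% interval for the difference is −8.8 to +28.5 points. The test finds nothing, yet the interval allows an excess of more than 25 points.

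**What a margin rule would deliver.** Suppose the true rate is 10.5% in both arms of 30 and no increase is concluded when the Newcombe upper limit is below the margin. By exact enumeration that happens in 18% of trials for a 10-point margin, 40% for 15 points and 66% for 20 points. The documents give no margin; these three are illustrations.

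**The case against.** **A reader might infer that the trial will treat a non-significant result as proof of safety, and will almost certainly report no increase.** No passage says so. The Hypothesis states an expectation, the test line is generic and allows exceptions, and the Discussion names the small sample as a limitation and calls for larger studies. On the numbers, chi-square would still detect a doubling from 10.5% in about one trial in five. Percentages will also be reported, and in that scenario SR shows the higher observed failure rate in 83% of trials. This objection stands: the misreading is a risk that the text leaves open, not a declared rule.

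**A margin or interval may sit in a fuller document.** True, and its absence from an article is not the point here. The point is that two stated items do not fit: a no-worse clause and a difference test as the only named analysis.

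**The reference rate is weak.** The 10.5% comes from children under a holiday protocol with up to four attempts. This trial's failure definition differs, covering HFNC re-application within 24 h of conversion, NIV or intubation. The protocol itself doubts that the study carries over to adults. This also stands, and is why 26% is shown beside it. The chance of missing a doubling depends on the rate; the inability of a non-significant test to support the clause does not.

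**A reader might also infer that the time result is settled by the schedule, leaving failure as the only open question.** In the SR arm "both flow and FiO_2_ will be gradually reduced simultaneously at a rate of 10 L/min and 0.1 /h", so if every step is tolerated SR needs the larger of the two step counts and the sequential arms need their sum. But each step requires the weaning criteria to be met, steps can be held, the starting flow is not given, and the primary outcome counts successful weaning. The documents do not show that the time result is fixed in advance.

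**Conclusion.** The point holds as a mismatch between the hypothesis and the stated test. A non-significant two-sided chi-square or Fisher result cannot support the failure clause at any reference rate. In size, at 30 per arm a doubling is missed about 80 to 90% of the time from 10.5%, and about half the time from 26%; the interval is about ±15.5 points at equal rates of 10.5%. Both rates are assumptions, because the documents give no adult HFNC weaning failure rate, and the figures assume pairwise comparisons.

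The severity is should-fix. Failure is a secondary outcome, the primary analysis is not affected, and the documents do not commit the investigators to the faulty inference.

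**What to change.** 1. Report the SR-minus-FR and SR-minus-OR differences in failure rate, each with a Newcombe 95% confidence interval.
2. Reword the failure clause of the Hypothesis as estimation: the trial will estimate the difference in failure rate between SR and each sequential strategy.
3. State that a non-significant p value will not be taken as evidence of no increase.
4. Allow the no-increase conclusion only if the upper confidence limit lies below a margin that the investigators justify before any outcome data are compared by arm. Recruitment began in January 2019, so a margin set now should be dated and described as set after the start but before any such comparison, if that is the case.

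The cost is a change of wording and one analysis line, with no extra patients. The downside is a more limited conclusion: if the true rates are equal at 10.5%, no increase could be concluded in fewer than half of such trials at a 10- or 15-point margin, and in about two thirds at 20 points. Estimation wording is therefore the realistic choice at this size. A powered non-inferiority comparison at the same rate (one-sided 0.025, 80% power) would need about 148 per arm for a 10-point margin or 66 for 15 points.

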### Study design and patients

This study is a prospective, investigator-initiated, randomized controlled study with three experimental groups. Patients aged over 18 years receiving respiratory support through a HFNC for any indication will be screened for study participation. Participants satisfying all weaning criteria, whether they are medical or surgical, will be prospectively recruited after providing written informed consent. The weaning criteria are as follows: patients who have recovered from their underlying condition, show no signs of respiratory distress (such as agitation, diaphoresis, or anxiety), with arterial pH ≥ 7.35, partial pressure of oxygen (SpO_2_) > 90% with FiO_2_ ≤ 0.5, respiratory rate ≤ 25 breaths/min, heart rate ≤ 120 beats/min, and systolic blood pressure (SBP) ≥ 90 mmHg. Patients will be excluded from the study if they have severe hypercapnia (pH < 7.25), respiratory arrest requiring tracheal intubation, cardiac arrest, acute coronary syndrome or life-threatening arrhythmias, or failure of more than two organs. Patients who have had recent trauma or burns to the neck and face, are pregnant, or who refuse to participate or cooperate in the study will be also excluded.

Informed consent will be obtained from the patients when they are ready to be weaned off the HFNC. However, if the patients cannot understand information about the study, remember the information, or communicate their decision by talking, using sign language, or any other means, they will be considered to be unable to make a decision. In that case, consent will be obtained from their families or the legal representatives.

### Randomization

A research coordinator will randomize the participants. An independent statistician will generate a list of random numbers. Eligible participants will be randomly assigned at a ratio of 1:1:1 to the flow reduction first (FR) group, the FiO_2_ reduction first (OR) group, or the simultaneous reduction (SR) group, in accordance with the predefined randomization list with a block size of 3. Information about the randomization will not be provided to the research supervisor, co-researcher, or patients. In the case of an emergency, co-researchers who are aware of the random assignments should avoid participating in future results analysis.

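### A single fixed block size of 3 for three usually recognisable arms makes up to a third of allocations deducible: an avoidable risk of selection bias, cheaply reduced

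*Protocol article*

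**What the plan says.** The Randomization section of the protocol article sets the ratio ("Eligible participants will be randomly assigned at a ratio of 1:1:1") and one block size: allocation is "in accordance with the predefined randomization list with a block size of 3". It names no other block size, and the article mentions no stratification.

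The roles are split. "An independent statistician will generate a list of random numbers", and "A research coordinator will randomize the participants". The stated safeguard is that "Information about the randomization will not be provided to the research supervisor, co-researcher, or patients". For emergencies, the section adds that "co-researchers who are aware of the random assignments should avoid participating in future results analysis".

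Types of interventions shows how the arms differ at the bedside. "In the FR group, flow will gradually be reduced by 10 L/min/h", with FiO2 following once flow has reached its target. The OR group takes the two settings in the opposite order. In the SR group, "both flow and FiO_2_ will be gradually reduced simultaneously". The Discussion asks the attending physician and nurse to assess the patient within 30 minutes of each change of setting, and says that the trial runs at a tertiary referral hospital.

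**The concern.** When the block size equals the number of arms, the last place in each block is fixed by the first two, and the second place is already narrowed to two arms. Keeping the list secret protects against this only if past assignments are also hidden. Here they mostly are not, because the intervention is the visible order in which two settings are turned down. With one hospital and, as far as the article says, one unstratified list, there is a single sequence to follow.

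What is at stake is who gets enrolled and when. Most entry criteria are numeric, but recovery from the underlying illness and absence of respiratory distress call for judgement, and consent is sought once the patient is thought ready. Someone who could foresee the next arm would have room to bring a patient forward or hold one back by some hours. The primary outcome is a time to weaning measured in hourly steps, so a small shift in readiness or starting settings could matter. Adjustment for baseline could deal with measured settings but not with unmeasured readiness.

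**Working it through.** **Inputs.** Three arms, 1:1:1, one block size of 3 (Randomization). Planned total 100, from 90 with 10% dropout (Sample size calculation). Arms distinguished by the order of lowering flow and FiO2 (Types of interventions). Recruitment January 2019 to December 2020 (Trial status). Article published 14 January 2020.

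**The plan's own figure.** 90 / (1 − 0.10) = 100, as stated. The article gives no figure for predictability.

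**Predictability with a fixed block of 3.** For an observer who knows the block size, the block boundary and all past assignments, the chance of a correct guess by place in the block is:

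- place 1: 1/3
- place 2: 1/2
- place 3: 1

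Average per block = (1/3 + 1/2 + 1)/3 = 11/18 = 61.1%, against 33.3% by chance.

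With 100 patients there are 33 full blocks plus one patient. So 33 allocations are fully determined, another 33 are narrowed to two arms, and expected correct guesses are 33 × 11/6 + 1/3 = 60.8, against 33.3 under simple randomisation.

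**When arms cannot always be read.** If FiO2 starts at 0.3, or flow starts at 20 L/min, only one setting is left to lower and all three arms follow the same visible course. The article does not say how often this happens. As an assumption, let each assignment be readable with probability r, independently. The third place is determined only if both earlier ones are readable, so the count is 33 × r². The average chance of a correct guess is the mean over the three places of:

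- place 1: 1/3
- place 2: r/2 + (1 − r)/3
- place 3: r² + r(1 − r) + (1 − r)²/3

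| r (assumed) | Determined per 100 | Correct guesses |
|---|---|---|
| 1.0 | 33 | 61% |
| 0.9 | 27 | 57% |
| 0.7 | 16 | 50% |
| 0.5 | 8 | 44% |

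**Alternatives.** These were simulated for 100 patients with an optimal guesser who sees every past assignment (r = 1). There were 5,000 runs where the size of each block is known and 1,500 where only the set of sizes is known.

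| Scheme | What the observer knows | Determined per 100 | Correct guesses |
|---|---|---|---|
| Fixed 3 | size | 33 | 61% |
| Fixed 6 | size | 19.2 | 56% |
| Fixed 9 | size | 14.2 | 53% |
| Random 3/6/9 | size of each block | 18.9 | 55% |
| Random 3/6 | set of sizes only | 8.6 | 58% |
| Random 3/6/9 | set of sizes only | 3.8 | 55% |
| Random 6/9 | set of sizes only | 5.0 | 54% |

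The main gain is in determined allocations. It depends on the size of each block staying unknown: 3.8 per 100 if it does, 18.9 if it does not.

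**Sensitivity of the outcome.** Read the entry criterion as FiO2 of at most 0.5, and suppose that every hourly step is passed on time. With *a* flow steps and *b* FiO2 steps, sequential weaning takes a + b hours and simultaneous weaning max(a, b). The difference is min(a, b), which cannot exceed b = (0.5 − 0.3)/0.1 = 2 hours. A starting flow 10 L/min lower saves 1 hour in FR or OR. Modest steering by starting settings could therefore be of the same order as the difference that the schedule itself produces.

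**Imbalance under the remedy.** An unfinished block of 3 can leave two arms differing by 1 patient. An unfinished block of 9 holds at most 3 of one arm and 0 of another, a difference of 3.

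**The case against.** A reader might infer that concealment has failed for a third of the patients. The article does not support that. Deduction requires one person who screens or seeks consent and who also knows the block size, the block boundary and both earlier assignments. The article does not identify such a person. It separates list generation from randomisation and withholds randomisation information from several roles. It does not say how assignments are released, which a condensed article may leave to the full protocol.

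Other points also stand:

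- The article appeared about halfway through the planned 24 months, so publication cannot have revealed the block size before then.
- At 100 patients in 24 months, about 4 a month, a block takes roughly three weeks. Patients are both medical and surgical, so the same clinicians may not see consecutive ones.
- Some patients' arms cannot be read, and one unreadable predecessor removes certainty about the third.
- The sentence about co-researchers who know assignments concerns emergencies, and is weak evidence of routine leakage.
- On overall guessing, varying the blocks moves the figure only from 61% to about 55%.

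All this limits how often prediction would succeed. It does not remove the weakness. Envelopes or a central system hide the next assignment from direct view, but not one that follows from two visible predecessors. The research coordinator, who randomises, is not among those from whom information is withheld.

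**Conclusion.** The point holds as a matter of avoidable predictability. The article fixes the most predictable block size possible for three arms, in a single-hospital trial whose arms can usually be recognised. Up to 33 of 100 allocations can be deduced, and up to 61% can be guessed correctly against 33% by chance.

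Both figures assume an observer who is involved in screening or consent, knows the block size and boundaries, and can read every earlier assignment. They also assume one unstratified sequence, which is what the article describes. If fewer assignments are readable, the figures fall as tabulated. The arithmetic is certain. How often anyone could use it is unknown, and no breach or bias is shown. The change is worth making because it costs little. The point does not invalidate the allocation of patients already randomised.

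**What to change.** For all remaining patients, have the independent statistician issue a new list with randomly varying block sizes, for example 3, 6 and 9. Do not disclose the sizes to site staff, including the research coordinator, and do not publish them until recruitment has ended. A larger fixed block is a weaker remedy: if its size is known, it still leaves about 19 (size 6) or 14 (size 9) determined allocations per 100.

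Even against an observer who knows the set of sizes, the varying list cuts determined allocations to about 4 per 100 and correct guesses to about 55%.

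The cost is one new list from a statistician already in place and a short amendment. If the new list starts where a block of the old one ends, the largest possible difference between two arms at the interim or the end rises from 1 patient to 3. No clinical procedure changes. If no patients remain to be randomised, the change is no longer available, and the fixed block size should be reported as a limitation.
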